## Abstract

**Background:**

Colorectal cancers are one of the most common forms of malignancy worldwide. But two significant areas of research less studied deserve attention: health services use and development of patient stratification risk tools for these patients.

**Methods:**

Design: a prospective multicenter cohort study with a follow up period of up to 5 years after surgical intervention. Participant centers: 22 hospitals representing six autonomous communities of Spain. Participants/Study population: Patients diagnosed with colorectal cancer that have undergone surgical intervention and have consented to participate in the study between June 2010 and December 2012. Variables collected include pre-intervention background, sociodemographic parameters, hospital admission records, biological and clinical parameters, treatment information, and outcomes up to 5 years after surgical intervention. Patients completed the following questionnaires prior to surgery and in the follow up period: EuroQol-5D, EORTC QLQ-C30 (The European Organization for Research and Treatment of Cancer quality of life questionnaire) and QLQ-CR29 (module for colorectal cancer), the Duke Functional Social Support Questionnaire, the Hospital Anxiety and Depression Scale, and the Barthel Index. The main endpoints of the study are mortality, tumor recurrence, major complications, readmissions, and changes in health-related quality of life at 30 days and at 1, 2, 3 and 5 years after surgical intervention.

Statistical analysis: In relation to the different endpoints, predictive models will be used by means of multivariate logistic models, Cox or linear mixed-effects regression models. Simulation models for the prediction of discrete events in the long term will also be used, and an economic evaluation of different treatment strategies will be performed through the use of generalized linear models.

**Discussion:**

The identification of potential risk factors for adverse events may help clinicians in the clinical decision making process. Also, the follow up by 5 years of this large cohort of patients may provide useful information to answer different health services research questions.

**Trial registration:**

ClinicalTrials.gov Identifier: NCT02488161. Registration date: June 16, 2015.

**Electronic supplementary material:**

The online version of this article (doi:10.1186/s12885-016-2475-y) contains supplementary material, which is available to authorized users.

## Background

Colorectal cancers are currently among the most common cancers in both women and men [1, 2]. Although many scientific approaches have been applied in this field, primarily with respect to diagnosis and treatment, two significant aspects require increased focus, the first of which is the development of clinical prediction rules to predict adverse events after surgical treatment of colorectal cancer patients. While some measurements of short-term outcomes have been developed, such as the different versions of the Physiological and Operative Severity Score for the enUmeration of Mortality and morbidity (POSSUM) scoring [3–5], most are not properly validated in other settings. Furthermore, prediction models for medium-term follow up (e.g., 1 or 2 years), a period in which the majority of adverse outcomes after treatments are observed, are inadequate. Not only robust clinical outcomes such as mortality, major complications, relapses or reinterventions should be studied and related factors identified, but also the determinants of changes in health-related quality of life, as perceived by the patient; these are referred to as patient reported outcome measurements (PROMs) [6–8]. The second significant area of research interest is related to health services research, where multiple factors remain unquantified. Among these are the quality of the health care process from the time that initial symptoms present in the patient to the time at which the patient receives treatment, equity in access to diagnosis and treatment procedures, provision of auxiliary support services (including key psychosocial services) or the cost and effectiveness of different surgical approaches [9–11].

Study protocol manuscripts are quite common in the cancer research field but mainly to present clinical trials of treatments for these patients. Less common, though no rare, other large and ambitious studies dealing with quality of care o even health services research have also published their study protocol. [12, 13].

### Study goals and objectives

The purpose of this study is to clarify some of the previously stated questions and unknown factors. The specific study objectives are displayed in Fig. 1 and are: 1. To determine risk factors for death or major complications, reoperations, or readmissions in the short-term; 2. To determine risk factors for death, tumor recurrence, major complications, readmission or deterioration in quality of life in the mid-term; 3. to evaluate patient reported outcomes from before intervention to the end of the follow-up period. 4. To evaluate the role of biological markers in the prediction of adverse results; and 5. from a health services research perspective, to evaluate equity, appropriateness, access to care, treatment cost, and psychosocial support for patients.

**Fig. 1 Fig1:**
[figure not shown]
Study objectives

With the purpose of reducing publication bias and improving reproducibility and to serve as reference for future manuscripts derived from this study and for readers we present the study protocol of this multicenter research work.

## Methods/design

### Study design

An observational analytic prospective cohort study with a planned patient follow up period of 5 years following surgical intervention.

Setting: patients recruited from 22 hospitals representing 9 provinces in Spain, all of which operate under the Spanish National Health Service (SNHS), which is responsible for the majority of the national population. All applicable residents have free access to their primary care physician and to the hospital ED. Participating hospitals are: Hospital de Antequera, Hospital Costa del Sol, Hospital Universitario de Valme, Hospital Universitario Virgen del Rocío, Hospital Universitario Virgen de las Nieves, Hospital Universitario de Canarias, Corporació Sanitaria Parc Taulí, Althaia, Hospital del Mar, Hospital Clínico San Carlos, Hospital Universitario La Paz, Hospital Infanta Sofía, Hospital Universitario Fundación Alcorcón, Hospital Galdakao-Usansolo, Hospital Universitario Araba, Hospital Universitario Basurto, Hospital Universitario Cruces, Hospital Hospitalario Donostia, Hospital Bidasoa, Hospital de Mendaro, Hospital de Zumarraga and Hospital Universitario Doctor Peset.

Research population: Patients diagnosed with colorectal cancer that underwent surgical intervention at one of the listed hospitals between June 2010 and December 2012. Patients were informed of the study objectives and invited to voluntarily participate. Patients were included in the study sequentially.

Expected duration of the study: patients will be followed until 5 years after the surgical index intervention, or until death.

#### Selection criteria

Patients will be deemed eligible for the study if they have undergone surgery for colorectal cancer in one of the participating hospitals. Colorectal cancer diagnosis is based on anatomopathological diagnosis after a biopsy by colonoscopy [10, 14, 15].

Inclusion criteria: diagnosis with colon cancer (up to 15 cm above the anal margin) and rectum (between the anal margin and 15 cm above it), where curative or palliative surgery by first time was applied. Exclusion criteria are colon or rectum in situ cancer, inoperable tumor, severe mental or physical condition which prevents the patient from responding to questionnaires, terminal illness, inability to respond to questionnaires for any reason, or lack of consent to participate in the study. Figure 2 illustrates a flow chart of the recruitment process. Recruitment data from participating hospitals as of December 2012 are provided in Table 1.

**Fig. 2 Fig2:**
[figure not shown]
Flow chart of the recruitment process

**Table 1 Tab1:** Recruited patients by area and hospital

Autonomous community	Hospital	Valid patients
		*n*
Andalucía	Antequera	41
	Costa del Sol	95
*n* = 490	Valme	137
	Virgen de las Nieves	31
	Virgen del Rocío	186
Canarias *n* = 101	Complejo Hospitalario de Canarias	101
Cataluña	Corporació Parc Taulí	332
*n* = 689	Althaia	100
	Hospital del Mar	257
Madrid	La Paz	169
	Infanta Sofía	64
*n* = 343		
	Clínico de San Carlos	39
	Alcorcón	71
País Vasco	Txagorritxu	88
	Bidasoa	33
	Donostia	245
	Mendaro	28
*n* = 998	Zumarraga	39
	Basurto	229
	Cruces	139
	Galdakao-Usansolo	197
Valencia *n* = 128	Doctor Pesset	128
Total		2749

### Methodology

Eligible patients were primarily identified from the surgical waiting lists of participating hospitals. For those receiving urgent surgery, identification took place during the hospitalization period. Depending on the hospital, one of two strategies were implemented for the inclusion of patients: a) surgeons or other healthcare professionals explained the study objectives and invited patients to voluntarily participate, during a clinical visit prior to surgery or during hospitalization for surgery; or b) written information about the goals of the study and the consent form for participation were sent to patients prior to hospitalization for surgery.

Following the patient selection process, clinical data and PROMs were collected at specific time points. Figure 3 summarizes the data-gathering process.

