IV	105 (3.93)	24 (3.20)	81 (4.21)
Surgical approach (main)			
Open surgery	1139 (41.89)	307 (40.55)	832 (42.41)
Laparoscopy	1580 (58.11)	450 (59.45)	1130 (57.59)
Laterality of the tumor (Right –transverse side)	834 (42.14)	NA	834 (42.14)
pTNM			
0, I, II	1581 (57.85)	485 (63.32)	1096 (55.72)
III	892 (32.64)	221 (28.85)	671 (34.11)
IV	260 (9.51)	60 (7.83)	200 (10.17)

Laterality of the tumor: Right-transverse side (appendix, cecum, ascending colon, right hepatic flexure and transverse) versus left side (left splenic flexure, descending colon, and sigmoid colon)

*ASA*, American Society of Anesthesiologists

*pTNM* pathological tumor-node-metastasis staging

^a^Means and, in brackets, standard deviation

Information was next collected through the first year of follow-up, including need for and type of treatment (separately evaluated for colon or rectal tumors), radiation therapy, chemotherapy (treatment schedule, neo or adjuvant therapy, number of cycles, presence and degree of treatment complications, and supportive care requirements), other medical treatments and psychological support. Information was also collected on laboratory and diagnostic tests performed, presence of complications, additional surgeries, tumor recurrence, readmission or reintervention, and death.

Information collected at the 2-, 3- and 5-year visits was similar to that of the 1-year visit.B.Patient reported outcomes measures (PROMs)

Patients completed the following questionnaires prior to surgery and in the follow up after surgery: EuroQol-5D (EQ-5D), EORTC QLQ-C30 (The European Organization for Research and Treatment of Cancer Quality of Life Questionnaire-C30) and QLQ-CR29 (European Organization for Research and Treatment of Cancer Questionnaire Module for Colorectal Cancer), the Duke-UNC Functional Social Support Questionnaire (FSSQ), the Hospital Anxiety and Depression Scale (HADS), and the activities of daily living (ADL) Barthel Index (BI).

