The Duke-UNC FSSQ questionnaire is composed of 11 items, each of which is rated on a five-point Likert scale ranging from 1 to 5: the higher the score, the better the perceived social support. It assesses subjective social support in two domains, Confidant support: 6 items (score range 6–30) and Affective support: 5 items (score range 5–25), and provides an overall social support measure (score range: 11–55) [27]. The questionnaire has been translated into and validated in Spanish [28].

The BI questionnaire consists of 10 items that assess the ability to perform certain basic activities of daily life without help. It includes 2- and 4-point response options that produce a score ranging from 0 (completely dependent) to 100 (completely independent), with intervals of 5 points [29]. The BI has been translated into and validated in Spanish [30].

Patients were first contacted upon inclusion in the surgical waiting list for a surgical intervention or were interviewed during their hospital admission period. Questionnaires were subsequently provided at 30 days, and at 1, 2, 3 and 5 years after surgery. In all instances, a reminder letter was sent to patients who had not replied after 15 days. Those who had not responded after a further 15 days received another reminder letter and, where feasible, contacted by telephone.

Questionnaires for the 30 day follow up visit were sent to patients attending the following hospitals: Hospital Costa del Sol, Hospital Valme, Hospital Virgen del Rocío, Hospital Virgen de las Nieves, Corporació Sanitaria Parc Taulí, Hospital Universitario La Paz, Hospital Infanta Sofía, Hospital Clínico San Carlos, Hospital Fundación Alcorcón, Hospital Basurto, Hospital Cruces, Hospital Donostia, Hospital Galdakao-Usansolo, Hospital Txagorritxu.

Figure 3 illustrates the data gathering process established for the entire follow-up period.

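### Patients may be enrolled and interviewed after the operation, so those enrolled late are selected on early survival and their baseline questionnaires may be post-operative

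*Protocol article*

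**What the plan says.** **Identification and invitation (Methodology).** Waiting lists are the main source. For the rest: "For those receiving urgent surgery, identification took place during the hospitalization period". Under strategy (a), patients are invited "during a clinical visit prior to surgery or during hospitalization for surgery", with no limit to urgent cases. Under strategy (b), written information and "the consent form for participation were sent to patients prior to hospitalization for surgery", which cannot serve an unplanned admission.

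**Eligibility (Selection criteria).** "Patients will be deemed eligible for the study if they have undergone surgery for colorectal cancer in one of the participating hospitals". Exclusions include "severe mental or physical condition which prevents the patient from responding to questionnaires" and "inability to respond to questionnaires for any reason, or lack of consent to participate in the study". No time point is given for judging either. The Ethics section requires written consent.

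**Time origin (Study design).** Follow-up lasts until five years after the index operation, or until death.

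**Baseline questionnaires (Data related to hospital admission, part B).** "Patients completed the following questionnaires prior to surgery and in the follow up after surgery". Later in the same part, patients were first contacted when placed on the waiting list "or were interviewed during their hospital admission period". The QLQ-C30 and HADS ask about the previous week.

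**Uses.** Objective 1 covers short-term death, major complications, reoperation and readmission. Objective 3 covers patient-reported outcomes from before the intervention onwards. The Data collection section says the POSSUM versions will be tested in this cohort. Anticipated issues lists loss to follow-up, missing data and reviewer reliability, but not selection at entry.

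**The concern.** Time zero is surgery, but for some patients the entry condition can be applied after time zero. A patient who dies, or remains sedated or too ill to answer, before being approached cannot consent and is not in the cohort. Entry then depends on the outcome that objective 1 sets out to predict, which is different from ordinary non-participation. The effect would be greatest where early risk is highest, which is also where the POSSUM scores are to be tested. The planned random split into derivation and validation sets would not reveal it, because both halves carry the same selection.

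The second issue concerns objective 3. If the first questionnaire was completed after surgery, its one-week recall covers the peri-operative period at least in part. Change measured from that point is not change from before the intervention. A later score could look like improvement when it is only a return to the pre-operative level. That direction is plausible, not certain.

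**Working it through.** **1. The plan's own figure.** The sample size section expects more than 300 events at a first-year mortality above 15%. With the 2749 recruited, 0.15 × 2749 = 412; 300 events would need 300 / 0.15 = 2000 patients. The figure reproduces and is not in dispute. The issue here is bias, which more patients would not remove.

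**2. Who can be lost, according to the text.**

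| Situation | In the cohort? |
|---|---|
| Approached and consented before surgery, then dies or deteriorates | Yes |
| First approached after surgery, alive and able to respond | Yes |
| Dies or becomes unable to respond before being approached | No |

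The third row can occur for urgent patients, and for elective patients invited during the admission under strategy (a).

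**3. Effect on the urgent-versus-elective odds ratio.** Let d be true urgent 30-day mortality, e elective 30-day mortality, and f the share of urgent deaths that occur before the approach.

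- Observed urgent mortality = d(1 - f) / (1 - df)
- Observed urgent odds = d(1 - f) / (1 - d)
- Observed odds ratio = true odds ratio × (1 - f), if no elective deaths are lost

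If a share g of elective deaths is lost as well, the factor becomes (1 - f) / (1 - g). With f = g the odds ratio is unchanged, but the absolute risk is still understated in both groups.

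The documents give none of d, e or f. With e = 2% and g = 0 **assumed**:

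| d (assumed) | True OR | f = 5% | f = 10% | f = 25% | f = 50% |
|---|---|---|---|---|---|
| 12% | 6.68 | 6.35 | 6.01 | 5.01 | 3.34 |
| 8% | 4.26 | 4.05 | 3.83 | 3.20 | 2.13 |

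Example: (0.12/0.88) / (0.02/0.98) = 6.68, and 6.68 × 0.75 = 5.01. The proportional fall equals f by construction, so the table illustrates the mechanism and does not estimate the bias.

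**4. Effect on overall 30-day mortality.** This also needs the urgent share u, which is not given. To end with 2749 enrolled, the source population is T = 2749 / (1 - u·d·f), and the deaths never enrolled are T·u·d·f. All inputs below are **assumed**, with e = 2% and g = 0:

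| u | d | f | Deaths not enrolled | True | Observed | Relative understatement |
|---|---|---|---|---|---|---|
| 5% | 5% | 25% | 1.7 | 2.15% | 2.09% | 2.8% |
| 10% | 10% | 50% | 13.8 | 2.80% | 2.31% | 17.4% |
| 20% | 20% | 50% | 56.1 | 5.60% | 3.67% | 34.4% |

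For f between 25% and 50%, with u and d each between 5% and 20%, about 2 to 56 early deaths would be missing. A smaller f gives less.

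**5. Baseline questionnaires.** One statement puts every baseline before surgery. Another allows first contact by interview at some point in the admission. Both are true only if every such interview took place before the operation, which the article does not say.

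**The case against.** Much of the opposing case stands, and it limits the point.

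- **Hospitalization includes the time before the operation.** A reader might infer that urgent patients who die early are excluded as a rule. The text does not support that: one who consents before surgery and dies during it is counted. The wording that patients have undergone surgery defines the population, not the moment of enrolment, since it also governs waiting-list patients.
- **The effect is not confined to urgent patients.** Strategy (a) and the interview wording are unrestricted. Elective losses would reduce the distortion of the odds ratio while still lowering absolute risk.
- **The two questionnaire statements are compatible.** A reader might call them a contradiction. They agree if every in-hospital interview was pre-operative. They leave timing open and need reconciling.
- **ASA and physiological predictors.** A reader might infer that these are weakened too. That is not shown. If urgent deaths are lost independently of ASA, the ASA odds ratio conditional on urgency in a logistic model is unchanged; only the intercept and the urgency term move.
- **This is a condensed article.** The recruitment and data-gathering figures and the instruction manual are not shown and may settle the timing. Even a count of missed patients, however, would not undo the selection.
- **Clinical baseline data come from records.** The baseline issue is therefore confined to the questionnaires.

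What remains is that entry, as written, may follow surgery, is conditional on being able to respond, and is paired with a surgical time origin.

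**Conclusion.** The point holds in a limited form. For any patient first approached after surgery, the stated rules select on early survival and ability to respond, while follow-up is counted from the operation. This can under-represent early deaths and severe complications in objective 1 and in the POSSUM tests, and Anticipated issues does not mention it. The documents do not give the number of patients affected, the urgent share, early mortality or the share of deaths before approach, so the size cannot be determined. The one general result is conditional: the urgent-versus-elective odds ratio is multiplied by (1 - f) if only urgent deaths are lost. Separately, a questionnaire completed after surgery is not the measurement that objective 3 assumes, and the two statements on its timing must be reconciled. Recruitment has finished, so the remedy lies in the analysis and in the scope of the claims.

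**What to change.** 1. **Classify** each patient by whether consent, and separately the baseline questionnaire, preceded surgery. Take the dates from the consent forms and questionnaires where available; the article does not say that they are recorded. Reconcile the two statements on questionnaire timing accordingly.
2. **Cox models:** for patients enrolled after surgery, use delayed entry at the consent date. State that this addresses deaths before consent but does not correct exclusion for incapacity.
3. **Objective 1 logistic models and POSSUM tests:** repeat them in pre-operatively enrolled patients as a pre-specified sensitivity analysis. Making this restriction the primary analysis is debatable, because it keeps only urgent patients fit enough to consent before the operation and so exchanges one selection for another.
4. **Objective 3 mixed models:** do not use a post-operative questionnaire as the pre-surgery baseline. Treat that baseline as missing, and include it only in a labelled sensitivity analysis.
5. **Claims:** limit statements on early mortality to the population that could be enrolled, and add this selection to the limitations.

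The cost is retrieving the dates and revising the analysis wording. The downside is fewer usable baselines, less precision for urgent patients and a narrower claim.

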**Fig. 3 Fig3:**
[figure not shown]
Data gathering process from baseline to 5 years of follow up. * Patient reported outcomes measures (PROMs) used: EuroQol-5D (EQ-5D), EORTC QLQ-C30 (European Organization for Research and Treatment of Cancer Quality of Life Questionnaire-C30); QLQ-CR29 (European Organization for Research and Treatment of Cancer Questionnaire Module for Colorectal Cancer), the Duke-UNC Functional Social Support Questionnaire (FSSQ), the Hospital Anxiety and Depression Scale (HADS), and the activities of daily living (ADL) Barthel Index (BI). Patient reported outcome at 30 days were collected in a sub-sample of the overall cohort and after 2 years in a selection of the original hospitals. ICU: Intensive Care Unit

